### Sample size calculations for main hypothesis

As the outcome of the primary study goal is predicted to be Arm 3>Arm 2>Arm 1, we compared both Arm 2>Arm 1, and Arm 3>Arm 2.

Our power calculations are based on the following assumptions: given an average size of a PHCU of approximately 15 000 adults, with an average of 1500 new consultations per month, we expect a cumulative coverage after 12 months of 0.0325 of the registered adult population to have had their alcohol consumption measured in the control condition (Arm 1) (data extrapolated from month 3 and month 9 assessments of control group from ODHIN study;^22 24^ [name], personal communication). For the short clinical package and short training (Arm 2), we expect this to increase to 0.075 (data extrapolated from month 3 and month 9 assessments of training group from ODHIN study;^22 24^ [name], personal communication). Although the WHO Phase IV study predicts an additional beneficial impact of municipal support,^41^ precise empirical data is not available—however, we consider an estimate for Arm 3, with municipal support, to be 0.15, a proportion that would need to be achieved to consider municipal support to be worthwhile. To detect the difference between Arm 2 and Arm 1, assuming a design effect of 15 PHCUs (clusters) across the three municipal areas in Arm 2, with 15 000 patients (items), and 12 PHCUs (clusters) in Arm 1, with 15 000 patients (items), with an ICC for PHCUs of 0.03 (data from ODHIN study;^22 24^ [name], personal communication) we would have 82% power at a significance level of 5%.^87^ For the difference between Arm 3 and Arm 2 (15 PHCUs/clusters in each arm), we would have 96.5% power.

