Within each intervention municipal area, a local Community Advisory Board (CAB) is created of key stakeholders, including representatives of local and regional government, directors of PHC services, non-governmental organisations active in providing counselling and treatment services for alcohol and mental health, academic experts and local media. The CABs meet regularly during the course of the study, giving advice on tailoring materials for local use, giving advice on adoption mechanisms, support systems and communication campaigns to support the action and preparing for sustainability and scale-up at the end of the action.

The units of allocation and analysis, that is, study participants, are 54 PHCUs and the providers working in them. Within each PHCU, eligible providers include any fully trained healthcare provider working in the PHCU and involved in medical and/or preventive care. Within each PHCU, individual providers decide themselves whether or not to participate in the study; those who do sign an informed consent for their participation. Based on the five-country ODHIN study, we estimate that approximately two-fifths of providers will consent to join the study.^61^ The overall study design is summarised in figure 1. Fifty-four PHCU are invited to join the study until 27 are achieved within each of the two municipal areas (intervention and control) across the three countries (nine per municipal area within each of the three countries).

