**Figure 1 F1:**
[figure not shown]
Study flow diagram.

Within each intervention municipal area, a user panel (UP) is created of providers and patients drawn from the PHC centres to advise on the tailoring of patient and provider materials and on provider training programmes.

For the first 6 months of the 18-month implementation and test period, a four-arm design is adopted, figure 2. Within the comparator municipal area, 12 PHCUs out of the 27 are randomly allocated to control (Arm 1), and 15 are allocated to receive short training to implement a short clinical package (Arm 2). Within the intervention municipal area, in which all 27 PHCU receive municipal action, 15 PHCUs are randomly allocated to receive short training to implement a short clinical package (Arm 3), and 12 PHCUs are allocated to receive standard training to implement a standard clinical package (Arm 4). Random allocation was undertaken using Excel random number generator.

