### Statistical tests of key hypotheses

#### Primary study goal

Multilevel regression analyses will be undertaken at 12 months’ time of the implementation test period, using cumulative results at months 1 to 12, and at 18 months’ time using cumulative results months 1 to 18. Both analyses will include covariates of country and results during baseline month, analysed at the levels of the PHCU by study arm, taking into consideration the hierarchical nature of the data. For any PHCU that drops out during the study, outcome values for subsequent measurement points will be set at the last value obtained.

##### Hypothesis 1

Municipal action leads to more sustainable coverage among PHCU that receive training. We will compare results on primary outcome after 18 months with results after 12 months between Arm 3 versus Arm 2 via regression.

Dependent variables:

For each PHCU, cumulative results of months 1–18 of number of patients whose alcohol consumption is measured with AUDIT-C per 1000 registered patients; and cumulative results of months 1–12 per 1000 registered patients.

Random effects:

Country as random intercept (test for inclusion).

Independent variables:

Proportion of consulting patients who have their alcohol consumption measured with a completed AUDIT-C instrument during the baseline measurement month.Condition:Municipal action (yes vs no).Covariate:Proportion of consulting patients who have their alcohol consumption measured with a completed AUDIT-C instrument during the baseline measurement month.

It is postulated that coverage for Arm 3 will be significantly higher than for Arm 2.

##### Hypothesis 2

Training leads to higher coverage than no training. For both months 1–12 and months 1–18, compare cumulative coverage as per primary outcome between Arms 1 and 2 via multilevel regression analyses.

Dependent variable

Cumulative results months 1–12, and cumulative results months 1–18 of number of patients whose alcohol consumption is measured with AUDIT-C per 1000 registered patients withPHCU.

Random effects:

Country as random intercept (test for inclusion).

Independent variables:

Condition:Training (Arm 2 vs Arm 1).Covariate:Proportion of consulting patients who have their alcohol consumption measured with a completed AUDIT-C instrument during the baseline measurement month.

It is postulated that coverage for Arm 2 will be significantly higher than for Arm 1.

##### Hypotheses 3

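### The 96.5% power for Arm 3 versus Arm 2, and the 5% error rate of its model, hold only if the two municipal areas within a country do not differ, an assumption the protocol does not state

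*Protocol article*

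**What the plan says.** **Design (Methods and analysis).** Intervention and control areas are chosen by the investigators in three cities; random selection was not feasible. PHCUs are recruited as "nine per municipal area within each of the three countries". The text after Figure 1 gives the level at which municipal action is applied: "Within the intervention municipal area, in which all 27 PHCU receive municipal action". Random allocation is between Arms 1 and 2 inside the control areas, and between Arms 3 and 4 inside the intervention areas. It never separates Arm 3 from Arm 2. The protocol nevertheless names the PHCU as the unit of both allocation and analysis.

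**Power (Sample size calculations for main hypothesis).** For Arm 2, "For the short clinical package and short training (Arm 2), we expect this to increase to 0.075"; for Arm 3, "we consider an estimate for Arm 3, with municipal support, to be 0.15". Clustering enters "with an ICC for PHCUs of 0.03", with about 15 000 adults per PHCU. The result is: "For the difference between Arm 3 and Arm 2 (15 PHCUs/clusters in each arm), we would have 96.5% power". These coverages belong to month 12. No area-level variance is given.

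**Model (Statistical tests of key hypotheses, Hypothesis 1).** Arm 3 is compared with Arm 2 with municipal action as the condition and the baseline-month proportion as covariate. The only random effect is "Country as random intercept (test for inclusion"). The introduction to that section mentions the hierarchical structure of the data in general terms. Propensity score matching on area and PHCU data is planned elsewhere.

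**The concern.** Every Arm 3 PHCU lies in one of three intervention areas and every Arm 2 PHCU in one of three control areas. For municipal action the comparison is therefore three areas against three, however many PHCUs each contains.

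PHCUs in one area share a health authority, local services and local politics. Whatever is common to an area and not removed by adjustment moves all its PHCUs together. Within a country, that shared part is indistinguishable from the effect of municipal action. A country intercept does not help, because it is common to both of the country's areas and cancels from the contrast between them.

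If such shared variation exists, the PHCU-level standard error is too small. The trial then has less power than stated, and a false positive for municipal action is more likely than 5%. Municipal action is a headline question of the study, and scale-up is foreseen once the strategy is validated.

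**Working it through.** **Inputs from the protocol:** coverage 0.075 (Arm 2) and 0.15 (Arm 3); 15 000 adults per PHCU; ICC 0.03; 15 PHCUs per arm; 5% level (two-sided reproduces the stated figures); three countries with two areas each.

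**Assumptions not in the protocol:** five PHCUs per area per arm (15 divided by 3; the split by country is not stated), and a ratio f of area variance within country to between-PHCU variance.

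**Step 1. Reproduce the stated power.**
- Design effect = 1 + (15 000 − 1) × 0.03 = 450.97.
- Variance of one PHCU's coverage = p(1 − p) × 450.97 / 15 000, which is 0.002086 for Arm 2 and 0.003833 for Arm 3.
- SE of the difference = √[(0.002086 + 0.003833)/15] = 0.01986.
- z = 0.075 / 0.01986 = 3.776; power = Φ(3.776 − 1.96) = 96.5%.

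The figure is reproduced, with 30 PHCUs as independent units, a normal reference and no area term.

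**Step 2. Take areas as units.** With five PHCUs per area per arm,

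SE² = Σ over the two arms of [f × PHCU variance / 3 + (PHCU variance + within-PHCU sampling variance) / 15].

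This is close to the Step 1 SE multiplied by √(1 + 5f). Power comes from the noncentral t distribution with noncentrality 0.075/SE. The reference is t on 4 df for six unpaired areas (critical value 2.776), or t on 2 df for three country pairs (critical value 4.303). The 4-df column also presumes that mean coverage does not differ between countries; pairing by country removes that requirement.

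**Step 3. Error rate of the PHCU-level test.** Null trials of 3 countries × 2 areas × 5 PHCUs were simulated and analysed with a PHCU-level t test without an area term, both with country omitted and with country as a fixed effect. The residual variance was re-estimated in each trial, so part of the area variance enters the fitted standard error.

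| f (assumed) | SE | Power, 4 df | Power, 2 df | Type I error, PHCU-level t test |
|---|---|---|---|---|
| 0 | 0.0199 | 80% | 53% | 5% |
| 0.05 | 0.0222 | 72% | 46% | about 7% |
| 0.10 | 0.0243 | 64% | 40% | about 10% |
| 0.25 | 0.0298 | 48% | 30% | 15–16% |

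In the top row the SE equals that of Step 1. The fall from 96.5% there comes only from having 4 or 2 degrees of freedom.

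**The case against.** **Area variance may be negligible.** If it is zero, the PHCU-level test keeps its 5% and the 96.5% stands. That is right, and a reader who infers that the figure is simply false goes further than the document allows, since it gives no area variance. But the protocol neither states nor defends this assumption.

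**The design already guards against area differences.** Control areas are selected for comparable socioeconomic characteristics and mental health services, the model adjusts for baseline-month measurement, and propensity score matching uses area and PHCU data. The limitations paragraph concedes that causality cannot be established as under randomisation. All this stands, and it means the relevant f is what remains after adjustment. It can make f smaller, but it adds no areas and no degrees of freedom.

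**The hierarchical structure is said to be considered.** The same sentence places the analysis at PHCU level by arm, and the random effect then listed is country alone.

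**The 53% belongs to a test the plan does not propose.** Correct. It should not be read as the trial's true power; the unpaired version gives 80% on the same inputs, and both need showing.

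**The 96.5% is not the power of Hypothesis 1.** Also correct. In the Introduction, Hypothesis 1 asks whether the gap between arms is larger at 18 than at 12 months, whereas the calculation concerns 12-month coverage. None of the figures above is a power or error rate for that change.

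**The 82% for Arm 2 versus Arm 1 might seem to fall with it.** It does not. Those arms are randomised within the same control areas, so the PHCU is the proper unit there, and the figure reproduces at 82.1%.

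**Conclusion.** The point holds in conditional form. The stated power and the nominal 5% error rate for the municipal contrast rest on an unstated assumption: no residual variance between the two areas of a country after baseline adjustment and matching. Keeping that assumption but taking the areas as units gives about 80% (4 df) or 53% (2 df) for the 12-month difference, instead of 96.5%. With area variance at 5% to 25% of PHCU variance, power runs from about 72%/46% down to 48%/30%, and the PHCU-level error rate from about 7% up to 15–16%.

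The range of f and the five PHCUs per area per arm are assumptions. That there are three areas against three, that the power calculation has no area component, and that the listed model has no area term can all be read directly in the protocol. Merging Arm 4 into Arm 3 from month 8 would add PHCUs to the intervention side but no areas.

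**What to change.** **In the sample size section:** state that the 96.5% refers to 12-month coverage and assumes no variance between areas within a country. Beside it, give the 4-df and 2-df area-level figures over a range of assumed area variances. Leave the 82% for Arm 2 versus Arm 1 as it is.

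**In the Arm 3 versus Arm 2 analysis:** report the three within-country area differences with a paired interval on 2 df beside the PHCU-level model. The alternative is a country-by-municipal-action random effect with small-sample degrees of freedom, though its variance would rest on about 2 df. State in advance that, if only the PHCU-level result is significant, the conclusion is limited to these three area pairs.

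**Cost:** some wording and one additional analysis. The stated power becomes less favourable and the interval for municipal action wider. No further PHCUs or data are required.

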### Patient and public involvement

Patients were not involved in the design of the study but are involved in the tailoring processes. Existing literature suggests that most patients find it acceptable for PHC providers to ask about their drinking using validated measurement instruments, and support the delivery of brief advice to those drinking above recommended levels.^88–96^ However, the majority of the evidence to date draws on research conducted in Europe, and thus the findings are potentially less transferable to Latin American populations. In order to ensure the design and content of the intervention package, including related outcome measures, are appropriate for implementation in the target SCALA sites, we work closely with patients in each city to tailor patient materials. Within the intervention municipal areas in each of the three countries, UPs are created with representatives of patients from the PHC centres. As part of the tailoring process, people and patients within the UPs have the opportunity to comment on the materials and information designed for use by patients. The results of the study will be disseminated directly to patients and the public through information made available via the PHCUs.

## Discussion

The study has several features worth mentioning. It:

Uses a theory-based approach^62–64^ to tailoring clinical materials and training programmes, creating city-based CAB, and user-based UPs to ensure that tailoring matches user needs, municipal services^97^ and coproduction of health.^98^Sets a higher cut-off score for AUDIT-C (8+) than is commonly used to trigger advice-giving, matching definitions of heavy drinking^99 100^ and similar to baseline levels of alcohol consumption in PHC-based trials to reduce heavy drinking.^52^ We set the same cut-offs for men and women, based on epidemiological evidence,^101^ and to minimise unintended consequences of using different cut-offs for men and women.^102^ We recognise the importance of comorbid depression by building in identification, management and referral mechanisms.^57–59^Tests for non-superiority of implementing a standard measurement and 5 min brief advice intervention with 6 hours of training, compared with implementing a shorter 1 min brief advice intervention with 3 hours of training, taking into account that brief advice is as effective and cost-effective as more extended advice or treatment in reducing heavy drinking^55 103 104^ and the need for very brief clinical and training programmes for time-constrained providers.Tests the added value of embedding and implementing PHC activity within municipal-based adoption mechanisms and support systems,^40^ and communication campaigns over and above training programmes solely directed to PHC providers.Has a longer time frame (18 months) than is traditionally used in implementation studies,^105 106^ to assess longer term impacts.Gives considerable emphasis to process evaluation,^79^ developing logic models to document the fidelity of all implementation strategies, and to identify, the drivers and barriers and facilitators to successful implementation and scale-up, and the political and economic contextual factors that might influence scale-up.

There are some limitations to the study design. A trial with random assignment of municipal areas is not feasible due to municipal-based political and technical considerations. As we are unable to randomise the involved municipal areas, we adopt a quasiexperimental design,^1^ trying to optimise control municipal areas for confounding, and by using PSM. While full comparisons via randomisation, and thus establishment of causality, are not possible, together with the qualitative evaluation component of the study, we will be able to clearly identify the mechanisms which were crucial in leading to the outcomes. According to a recent seven-item checklist for classifying quasiexperimental studies for Cochrane reviews,^107^ our approach is, nevertheless, ranked as a strong design, online supplementary table S7.

Although our focus on embedding PHC activity within supportive municipal actions is hypothesised to increase measurement and brief activity over and above that previously demonstrated, such an approach also brings risks. Municipal and national governments change; and, thus health priorities may change. Although our approach minimises the need for extra resources (and in some jurisdictions, could be resource saving),^19^ it is not resource free. Funding constraints could limit future scale-up and sustainability.

We have based our protocol adopted on a model of transdisciplinary research to promote sustainability. Such a model identifies, structures, analyses and deals with specific problems in a way that grasps the complexity of problems;^108^ it takes into account the diversity of real-world and scientific perceptions of problems; and develops knowledge and practices that promote what is generally accepted to be the common good.^109^ As such, we include municipalities and health systems as stakeholders to form explicitly orchestrated and managed ecosystems that cross-organisational boundaries. Municipal areas and health systems create an engagement platform that provides the necessary environment, including people and resources, for sustainability.

## Ethics and dissemination

This protocol outlines a quasiexperimental study^1^ to test the extent to which embedding PHC-based measurement and brief advice activity within supportive municipal action leads to improved scale-up of an intervention package, with more patients having their alcohol consumption measured, and with heavy drinkers receiving subsequent appropriate advice and treatment. It is not envisaged that there will be any substantial protocol modifications during the course of the study. Any modification to the protocol will be described in all scientific publications.

All participating PHCUs and participating PHC providers sign an informed consent form for participation with the country-based research team. Selected patients at two separate time points sign an informed consent form with the country-based research team to provide additional anonymised information following a consultation with a PHC provider. The consent forms are included within Annexe Data Management Plan. All data collection, processing, and sharing procedures will adhere to national and international laws including the General Data Protection Regulation (EU Regulation 2016/679), as described within the Annexe Data Management Plan.

All materials are publicly available on the project website: https://www.scalaproject.eu/. According to the SCALA data management plan, by default, all quantitative data sets generated in the course of the SCALA study will be made openly available through the UK Data Service on publication of the results (http://www.data-archive.ac.uk/). Prior to publication, all data will be formatted to meet UK Data Service requirements.

Ministries of Health at municipal and country levels are represented in the CAB created in each intervention municipality to facilitate scale-up at municipal and country levels, once the implementation strategy is validated. SCALA works closely with the Pan American Health Organization (PAHO), with the principal investigator form Mexico being a Collaborating Centre with PAHO, to facilitate scale-up at Latin American levels, once the implementation strategy is validated.
